### Assessment battery

Online supplemental table S1 presents our assessment battery including validated instruments measuring demographics; ARFID symptoms; other ED pathology; food intake; co-occurring psychiatric, neurodevelopmental, and somatic conditions and traits; treatment utilization; environmental exposures; impairment and quality of life; and parental stress and ED pathology. All mandatory assessments are parent-reported; additionally, we offer optional questionnaires to be completed by parents and adolescents. Completion of the entire assessment battery will take approximately 90 minutes and can be done across several sittings. Questionnaires are applied in Swedish and have been adapted for administration via Forsta (previously Confirmit).

### Case definition

Cases will be participants who screen positive for ARFID on the PARDI-AR-Q or NIAS, report no clinically significant disordered eating behaviours in the last 28 days that could suggest the presence of AN or BN on PEDE-Q and have no lifetime diagnosis of AN or BN. Controls will be participants who screen negative for ARFID on PARDI-AR-Q and NIAS, report no clinically significant disordered eating in the last 28 days suggesting the presence of AN or BN on PEDE-Q, have no lifetime diagnosis of any ED or other psychiatric condition, and who have no first-degree relatives with an ED as reported by the parent. Case participants who will be included in the microbiome substudy will display exceptionally high scores on the PARDI-AR-Q subscale for sensory-based food avoidance (see table 1), and control participants will display exceptionally low scores on all PARDI-AR-Q and NIAS subscales. Table 1 presents detailed inclusion and exclusion criteria for cases and controls included in the main study and in the microbiome substudy.

**Table 1 T1:** Inclusion and exclusion criteria for the main study and the microbiome substudy

	Main study		Microbiome substudy	
	Cases	Controls	Cases	Controls
NIAS	PE>9 **OR** LA>8 **OR** F>9	PE≤9 **AND** LA≤8 **AND** F≤9		PE<5 **AND** LA≤1 **AND** F≤1
	**OR**	**AND**		**AND**
PARDI-AR-Q	A0 met **AND** (A1 **OR** A2 **OR** A3 **OR** A4) met	A0—A4 not met	S>5.5*	S≤1 **AND** LA≤1 **AND** F≤1
	**AND**	**AND**	**AND**	**AND**
EDE-Q	Global score <4 **AND** No vomiting **AND** No laxative use	Global score <4 **AND** No vomiting **AND** No laxative use **AND** <5 binge eating episodes		
	**AND**	**AND**		
Control questions	No lifetime diagnosis of AN or BN	No lifetime diagnosis of any ED **AND** No first degree relative with a lifetime diagnosis of any ED **AND** No current diagnosis of a psychiatric disorder	No antibiotics or probiotics during the last 3 months **AND** Never hormones for gender reassignment **AND** No current inflammatory GI condition	No antibiotics or probiotics during the last 3 months **AND** Never hormones for gender reassignment **AND** No current inflammatory GI condition

* Due to the dominance of sensory-based food avoidance in children with ARFID^69^ and in order to obtain a sufficient sample size for microbiome analyses, we focused our microbiome analysis on those with high scores on S to investigate the association of sensory-based food avoidance with the gut microbiome.

AN, anorexia nervosa; ARFID, avoidant/restrictive food intake disorder; BN, bulimia nervosa; ED, eating disorder; EDE-Q, Eating Disorder Examination Questionnaire; F, fear score; GI, gastrointestinal; LA, low appetite score; NIAS, Nine Item ARFID Screen; PARDI-AR-Q, Pica, ARFID, and Rumination Disorder Interview-ARFID Questionnaire; PE, picky eating score; S, sensory-based food avoidance score.

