##### Hypotheses

Most participants with ARFID will show early childhood onset and a persistent course of illness. Furthermore, we expect participants with ARFID to report more co-occurring psychiatric, neurodevelopmental and somatic conditions than participants without ARFID. In terms of ARFID presentations, we expect to find sensory-based food avoidance to be related to autism, low appetite to depression and metabolic factors, and fear-based avoidance to anxiety and OCD.

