### Procedure

Parents/guardians of children and adolescents with ARFID who are interested in participation will be referred to the study website (www.ariesstudy.se) that provides detailed study information and contact details in case of questions (‘parents/guardians’ will henceforth be referred to as ‘parents’ for readability). To be eligible for participation, all individuals must have a valid Swedish personal number (a unique national identification number), which is required for both providing consent and linking to the Swedish National Health Registers. Study information is provided in three versions: for children (6–11 years), for adolescents (12–14 years), and for parents. If interested in participation, parents can register their child and provide online informed consent on the study’s website. Parents will complete online screening questionnaires covering ARFID and other disordered eating cognitions and behaviours including the Pica, ARFID and Rumination Disorder Interview-ARFID Questionnaire (PARDI-AR-Q),^47^ the Nine Item ARFID Screen (NIAS)^48^ and the parent version of the Eating Disorder Examination Questionnaire (PEDE-Q).^49^

The online screening questionnaires will be used to create a diagnostic algorithm for DSM-5 ARFID and determine eligibility and case status of the child. If the child is eligible for the study by parent-report, parents are instructed to complete additional questionnaires (some are mandatory, some are optional; online supplemental table S1). Additionally, we implemented optional self-report questionnaires for adolescents. A saliva sample collection kit including return packaging is mailed to the parent’s address with directions for saliva collection from the child. Those participating in the microbiome substudy will also receive a stool collection kit. Participation in the main study will be complete as soon as the kits are received by Karolinska Institutet (KI) Biobank and all mandatory questionnaires are completed. All participants receive two cinema tickets as soon as participation in the main study is complete. We do not provide participants in the microbiome substudy with additional reimbursement.

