### Additional data sources

Our data will be linked to nationwide Swedish health registers including the National Patient Register (NPR),^43^ the Prescribed Drug Register (PDR),^45^ the Medical Birth Register^44^ and the National Quality Register for Specialised Eating Disorder Treatment (Riksät/Stepwise).^46^ Register linkage is conducted by government agencies via the Swedish personal number. The NPR provides data on all inpatient care since 1987 and around 80% of specialised outpatient care since 2001,^43^ using International Classification of Diseases 10th revision classification since 1997. We will use the NPR to identify ARFID-related diagnoses; other EDs and psychiatric, neurodevelopmental and somatic conditions; as well as to track healthcare utilisation over time. Evidence shows strong agreement between ED diagnoses in the NPR and in Riksät/Stepwise, confirming the validity of NPR data for research.^53^ The PDR provides data on all drug prescriptions dispensed since 2005, with active drug ingredients categorised using the Anatomical Therapeutic Chemical (ATC) Classification System.^45^ We will use ATC codes to identify prescribed nutritional supplements and enteral nutrition relevant to ARFID and medication utilisation over time. Riksät/Stepwise contains data on ED treatment from around 100 specialised and general psychiatry units across 21 regions since 1999. We will extract diagnoses and clinical characteristics, such as symptom severity and impairment. Riksät offers broader coverage and includes DSM-IV subtypes, providing more extensive information than the NPR.^46^

For GWAS, we will combine our data with other completed, ongoing and planned collections conducted by PGC-ED. Refer to table 2 for the expected sample sizes at the time of analysis.

**Table 2 T2:** Sample sizes and availability of genotypes for the ARFID-GWAS meta-analysis

Study	Cases	Controls	Age	Available by
ASTRI	300	⁓18 000	6–12	Available
ARIES	1500	500	6–14	May 2025
ARFID-GEN	⁓3000	/	6–99	September 2024
EDGI2	⁓3000	⁓1300	15–99	March 2026
PGC-ED	1200	⁓42 000	15–99	Available

ARFID, avoidant/restrictive food intake disorder; ARFID-GEN, ARFID–Genes and Environment; ARIES, ARFID InitiativE Sweden; ASTRI, ARFID in the Swedish Twin Registry Initiative; EDGI2, Eating Disorders Genetics Initiative 2; GWAS, genome-wide association studies; PGC-ED, Eating Disorders Working Group of the Psychiatric Genomics Consortium.

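### Main-study case rule does not separate ARFID from restriction explained by a somatic disease, so part of the hypothesised somatic excess in cases may come from case selection

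*Protocol article*

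**What the plan says.** The case rule is in the protocol article, section Case definition: "Cases will be participants who screen positive for ARFID on the PARDI-AR-Q or NIAS, report no clinically significant disordered eating behaviours". The remaining condition is "no lifetime diagnosis of AN or BN". The article treats this as its full rule: "Table 1 presents detailed inclusion and exclusion criteria for cases and controls included in the main study and in the microbiome substudy".

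In Table 1, a main-study case needs either of the following:
- NIAS picky eating above 9, low appetite above 8 or fear above 9; or
- PARDI-AR-Q A0 together with any of A1 to A4.

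The eating-disorder questionnaire limits and the AN/BN history question then apply. No somatic or medication criterion appears in that column. The somatic and drug exclusions, among them "No current inflammatory GI condition", stand only in the two microbiome columns. Main-study controls must be at or below all three NIAS cut-offs and must not meet A0 to A4.

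The Procedure section says of the screen: "The online screening questionnaires will be used to create a diagnostic algorithm for DSM-5 ARFID and determine eligibility and case status of the child". Under Aim 1 the hypothesis is: "we expect participants with ARFID to report more co-occurring psychiatric, neurodevelopmental and somatic conditions than participants without ARFID". The Data analysis section plans generalised linear models for the case-control comparisons and names age and sex/gender as covariates.

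Under Additional data sources, the National Patient Register (NPR) is to supply somatic diagnoses. For the Prescribed Drug Register (PDR) the article says: "We will use ATC codes to identify prescribed nutritional supplements and enteral nutrition relevant to ARFID and medication utilisation over time". It states no use of either register to check or reclassify case status.

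**The concern.** The rule records how and how severely a child restricts, and not why. Take a child who eats little because of a chronic bowel disease, or who fears eating because of a known food allergy. If that child's parent-reported NIAS score passes the low-appetite or fear cut-off, the child becomes an ARFID case and is then counted as a case with a co-occurring somatic condition. The condition that produced case status is also the outcome being compared. The same score keeps the child out of the control arm. Both effects push the Aim 1 somatic contrast upwards, even if ARFID proper is unrelated to the condition.

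At stake is the interpretation of a positive somatic result. As planned, it could not be told apart from the effect of the entry rule. The same children would also sit among the GWAS cases and in the low-appetite and fear presentations, which the article wants to relate to other traits.

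**Working it through.** **The plan's own figure.** The document gives no number for this point. Its phenotypic sample size is 394 per group for an effect of 0.2 with 80% power. The normal formula gives 2 × (1.96 + 0.84)² / 0.2² ≈ 393, and the t-based version gives 393.4, rounded up to 394. Both use two-sided alpha 0.05. The printed alpha of 0.5 does not reproduce 394 (the normal formula gives 115) and is a separate matter. With 1500 cases and 500 controls, power for 0.2 is about 97%, so the comparison will also pick up modest selection artefacts.

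**Inputs.**
- From the document: 1500 cases, 500 controls.
- Assumed: p, the prevalence of the somatic condition in controls (5%, 10%, 20%); f, the share of cases that qualify only because of it (1% to 20%); true odds ratio 1 among the other cases.

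**Formulas.** Apparent prevalence in cases: q = f + (1 − f)p. Apparent odds ratio: OR = [q/(1 − q)] / [p/(1 − p)]. The standard error of log OR is √[1/(1500q) + 1/(1500(1 − q)) + 1/(500p) + 1/(500(1 − p))].

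**Example, p = 5%, f = 5%.** 75 of 1500 cases qualify because of the condition. Of the other 1425, 5% have it by coincidence, which is 71.25. So q = 146.25/1500 = 9.75%. OR = (0.0975/0.9025)/(0.05/0.95) = 2.05. SE = √(0.0068 + 0.0007 + 0.0400 + 0.0021) = 0.223, and z = 0.719/0.223 = 3.23.

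For f = 2%, q = 6.9%, OR = 1.41 and z = 1.49. For f = 10%, q = 14.5%, OR = 3.22 and z = 5.37.

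**Range.** Each cell gives the apparent OR and, in brackets, the chance of a significant difference (two-sided 0.05, 500 v 1500, before any multiplicity correction).

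| f | p = 5% | p = 10% | p = 20% |
|---|---|---|---|
| 1% | 1.20 (11%) | 1.10 (8%) | 1.05 (6%) |
| 2% | 1.41 (31%) | 1.20 (19%) | 1.10 (11%) |
| 5% | 2.05 (94%) | 1.53 (74%) | 1.26 (45%) |
| 10% | 3.22 (about 100%) | 2.11 (99.9%) | 1.56 (95%) |
| 20% | 6.00 (about 100%) | 3.50 (about 100%) | 2.25 (about 100%) |

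An 80% chance of a significant excess made by selection alone needs f of about 3.9% (59 cases) at p = 5%, 5.4% (81) at p = 10% and 7.7% (115) at p = 20%.

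**What removing flagged cases does.** If a share g of the cases with the condition is removed and no controls are, the case odds, and so the OR, are multiplied by (1 − g). In the example, removing exactly the 75 leaves 71.25 with and 1353.75 without the condition, and OR = 1. If the flag also removes half of the 71.25, OR falls to 0.5. Likewise, with g = 50% a true OR of 2 becomes 1.0. The restricted analysis is right only if the flag picks exactly the selection-made cases.

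**The case against.** **The consequence is unproven.** A reader might infer that the somatic excess is, at least in part, an artefact. The document does not support that, because it gives neither f nor any prevalence. At f of 1% to 2% the apparent OR is only 1.05 to 1.41. Recruitment is addressed to parents of children with ARFID, and the Table 1 footnote says that sensory-based avoidance dominates in children, whereas the examples here work through low appetite and fear. Both may keep f low. On the other side, the recruitment channels include paediatric services. Multiplicity correction is planned, but z = 3.23 (p about 0.0012) would survive a Bonferroni correction for about 40 tests. This objection stands as to size. It does not remove the gap.

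**The instruments may already handle medical causes.** The PARDI-AR-Q and NIAS items are not shown, and that ill children would pass the cut-offs is itself an assumption. But an exclusion within the PARDI-AR-Q would not bind a child who enters on NIAS alone.

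**Neurodevelopmental conditions.** A reader might extend the point to these, through drugs for such conditions that reduce appetite. The document states no such drug effect, and the calculations concern a somatic condition only. The psychiatric selection that the document does show acts on controls, who must "have no lifetime diagnosis of any ED or other psychiatric condition, and who have no first-degree relatives with an ED as reported by the parent". That is a different issue.

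**The restricted analysis as the answer.** A reader might conclude that the claim should rest on the analysis without flagged cases. That analysis selects on the outcome in one arm and could erase a true excess.

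**Disclosure and the analysis plan.** The article discloses its reliance on parent report in place of clinical diagnosis, and its hypothesis concerns co-occurrence, not causation. Code lists and sensitivity subsets commonly belong in the analysis plans, which are not shown. That is fair for the details. However, the case rule itself is fixed here, and the disclosed limitation does not say that a somatic disease could produce case status.

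**Conclusion.** The main-study case rule has no criterion separating ARFID from restriction explained by a somatic disease, and a NIAS low-appetite or fear score alone makes a case. Any such cases raise the somatic prevalence in the case arm by f(1 − p), so part of the hypothesised somatic excess may come from case selection. The size is unknown. With an assumed 5% control prevalence and a true OR of 1, shares of 2%, 5% and 10% give apparent ORs of 1.4, 2.1 and 3.2. The effect is small at 1% to 2%. It becomes likely to yield a significant result at roughly 4% to 8% for assumed control prevalences of 5% to 20%. Any effect on the GWAS and the presentation analyses has not been quantified. The point calls for a labelled sensitivity analysis and careful wording of the conclusion. Recruitment need not change.

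**What to change.** - Pre-specify a list of restriction-causing somatic diagnoses and relevant dispensed medicines. Using the planned questionnaires and the NPR/PDR linkage, flag cases in whom one of these precedes or coincides with the reported onset of restriction.
- Report the somatic case-control comparison with all cases and without flagged cases, as approximate upper and lower bounds. State that the restricted analysis is biased downwards because it removes cases by outcome in one arm only. The bounds are approximate because the flag can also miss cases; the article itself puts NPR coverage of specialised outpatient care at around 80%.
- Do not claim a somatic excess as a feature of ARFID from the all-case analysis alone.
- Run the GWAS and the low-appetite and fear presentation analyses with and without flagged cases, as a sensitivity analysis.

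The cost is a code list, analysis wording and some extra runs, with no new data collection. The downside is fewer cases in the restricted analyses, where some genuine ARFID cases with somatic illness are set aside.

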ARFID is present in 1%–2% of the general population^5 6^ and was formally recognised in 2013.^7^ ARFID is a feeding and eating disorder characterised by an extremely restricted dietary quantity or variety resulting in significant weight loss, nutritional deficiencies, reliance on nutritional supplements and/or psychosocial impairment.^7^ In contrast to other EDs, ARFID occurs in approximately equal proportions of males and females,^6 8^ has an earlier age of onset^9^ and the restrictive eating is not primarily motivated by weight and shape concerns.^7^ ARFID is often accompanied by severe and sometimes life-threatening somatic and psychosocial comorbidities, leading to high social and financial burden for patients and their families.^10^,^14^ Despite the significant impairment, our knowledge on ARFID aetiology is limited. In part due to this insufficient understanding, evidence-based treatments are only starting to be developed^15^ and no specific treatment guidelines exist.^16^ A longer duration of untreated EDs other than ARFID has been found to decrease the likelihood of recovery.^17^ It is, therefore, likely that the lack of treatment options significantly contributes to the chronicity of ARFID.

ARFID is conceptualised as a single disorder; however, the Diagnostic and Statistical Manual of Mental Disorders fifth edition (DSM-5) describes three non-mutually exclusive presentations: (1) sensory-based food avoidance; (2) low appetite or interest in food and (3) fear of aversive consequences of eating. These symptom clusters overlap in a subset of individuals with ARFID (15%–51%).^818^,^20^ Comorbidities vary somewhat depending on the dominant presentation(s)^11 19^; for instance, sensory-based food avoidance has been shown to be more strongly related to neurodevelopmental conditions, low appetite or interest in food to mood disorders,^21^ and fear of aversive consequences to obsessive-compulsive disorder (OCD) and anxiety disorders.^11^

ARFID-related phenotypes such as appetite, food fussiness and food neophobia have been shown to be moderately to highly heritable.^22^,^25^ Our previous research using Swedish twin data further supports our aim of conducting a GWAS for ARFID: with a twin-based heritability of 70%–85%,^5^ ARFID is among the most heritable of EDs^26^ and of psychiatric conditions in general.^27^,^30^

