#### Hypotheses

ARFID will share a core set of genetic factors with other EDs and be differentiated by disorder-specific genetic factors. ARFID will show the strongest genetic overlap with AN.

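### Table 1 lets undiagnosed, non-purging restriction driven by weight or shape concerns enter as ARFID; this biases the Aim 3 ARFID–AN genetic correlation upward, probably by little

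*Protocol article*

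**What the plan says.** The Background separates ARFID from other eating disorders by motive: in ARFID, "the restrictive eating is not primarily motivated by weight and shape concerns". The Procedure section says the parent-completed screens feed an algorithm for DSM-5 ARFID that decides eligibility and case status.

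The Case definition section asks that cases "report no clinically significant disordered eating behaviours in the last 28 days that could suggest the presence of AN or BN on PEDE-Q". A further condition in the same section concerns earlier diagnoses: "no lifetime diagnosis of AN or BN". Table 1 gives the working rule for main-study cases:

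- **ARFID screen.** Either NIAS, "PE>9 OR LA>8 OR F>9", or PARDI-AR-Q, "A0 met AND (A1 OR A2 OR A3 OR A4) met". The two instruments are joined by OR.
- **EDE-Q row.** "Global score <4 AND No vomiting AND No laxative use".
- **Control questions.** No lifetime AN or BN diagnosis.

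Aim 3 states the hypothesis that "ARFID will show the strongest genetic overlap with AN". Under Additional data sources, the National Patient Register (NPR) will be used to identify other eating disorders, and diagnoses will be extracted from Riksät/Stepwise. The article does not tie either source to the case exclusion.

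**The concern.** The text promises to exclude behaviour suggestive of AN or BN, but the only behaviours Table 1 names for cases are vomiting and laxative use. Motive for restriction enters only through a global score. A child with undiagnosed restricting AN need show neither behaviour, and a low intake can resemble low appetite on the NIAS. The mandatory assessments are parent-reported and adolescent self-report is optional, so a motive hidden from the parent may not raise the score.

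Any AN cases labelled as ARFID carry AN liability into the ARFID GWAS. That raises the ARFID–AN genetic correlation, which is the direction Aim 3 predicts, and weakens the contrast in the case-versus-case and disorder-specific analyses. A positive Aim 3 result would then be partly open to a misclassification explanation that the article gives no means of checking.

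**Working it through.** **Step 1: does the rule leave a gap?** Take a child who restricts because of weight or shape concerns, does not vomit or use laxatives, and has no AN or BN diagnosis.

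- ARFID screen: a NIAS low-appetite score above 8 is enough. The article does not give the content of PARDI-AR-Q criterion A0, which may ask about weight or shape, but the OR means the NIAS route bypasses it.
- Vomiting, laxatives, diagnosis: passed by construction.
- "Global score <4": the only remaining barrier.

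The documents do not describe how the global score is built. Assume it is the mean of four subscales, each scored 0–6. With weight and shape concern both at the maximum, the child passes if (6 + 6 + a + b)/4 < 4, that is, if the other two subscales sum to a + b < 4. So even maximal weight and shape concern need not trigger the exclusion.

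**Step 2: how much of the meta-analysis is ARIES?** Table 2 cases: 300 + 1500 + 3000 + 3000 + 1200 = 9000, which reproduces the figure under Statistical power. ARIES is 1500/9000 = 16.7%, or one sixth.

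**Step 3: effect on the genetic correlation.** Inputs not in the documents, and therefore assumed:

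- p, the share of ARIES cases who really have AN: 5%, 10%, 15%;
- r, the true ARFID–AN genetic correlation: 0 or 0.20;
- equal heritabilities;
- no contamination in the other cohorts, and weighting by case count.

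The contaminated share of all cases is m = p × 1500/9000 = p/6, and

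r_obs = [(1 − m)r + m] / √[(1 − m)² + m² + 2m(1 − m)r].

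Example, p = 10% (150 ARIES cases), r = 0.20: m = 0.0167; the numerator is 0.1967 + 0.0167 = 0.2133; the denominator is √(0.9669 + 0.0003 + 0.0066) = 0.9868; r_obs = 0.216.

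| p in ARIES | m overall | r_obs if r = 0.20 | r_obs if r = 0 |
|---|---|---|---|
| 5% | 0.83% | 0.208 | 0.008 |
| 10% | 1.67% | 0.216 | 0.017 |
| 15% | 2.50% | 0.224 | 0.026 |

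**Step 4: sensitivity to equal heritabilities.** Let k be the ratio of the AN to the ARFID genetic standard deviation, and replace m by mk in the AN terms. At p = 10% and r = 0.20, k = 0.7 gives 0.211 and k = 1.4 gives 0.223. In every scenario computed the shift is upward; its size depends on p, which is unknown.

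**The case against.** The strongest reply is that the effect is small and partly disclosed. The children are aged 6–14, their families are reached with ARFID-specific material, and the note to Table 1 says sensory-based avoidance dominates at this age, so undiagnosed AN may be rare. The article states openly that it relies on parent report rather than clinical diagnosis, and says why. It refers to predetermined analysis plans that are not shown, where sensitivity runs may be specified. All of this stands and limits the size of the problem. It does not close the gap, because Table 1 is presented as the detailed inclusion and exclusion criteria, so the case rule itself is fixed in this document.

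A reader might infer more than the documents support, in three ways.

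- **A large inflation.** If the formula is applied to ARIES alone, a true 0.20 becomes 0.25, 0.30 and 0.36 at 5%, 10% and 15%. But no ARIES-only ARFID–AN correlation is planned. The ARIES-alone GWAS is described as within-disorder, and the Discussion puts cross-disorder work on the combined ARIES/PGC-ED data.
- **No barrier except the global score.** Vomiting, laxative use and a lifetime AN or BN diagnosis also exclude. The gap is confined to undiagnosed, non-purging restriction.
- **A bias that favours the study's hypotheses throughout.** Aim 4 expects ARFID's genetic links with neurodevelopmental conditions and anxiety to exceed those with other eating disorders. AN contamination would work against that prediction.

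**Conclusion.** The concern holds in a limited form. As written, Table 1 can admit weight- or shape-driven restriction as ARFID when it is undiagnosed, non-purging and below a global score of 4. This conflicts with the Background's description of the disorder and with the aim stated in the Case definition text. The resulting bias in the ARFID–AN correlation is upward, towards the Aim 3 hypothesis.

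On the planned combined data the expected shift is small: from 0.20 to about 0.21–0.22 for 5–15% contamination in ARIES. This rests on an assumed contamination rate, equal heritabilities, weighting by case count, and clean case groups in the other cohorts, whose case rules the article does not describe. The point deserves correction because the direction favours a stated hypothesis and the data needed to check it are already planned, not because a large distortion has been shown.

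**What to change.** 1. Apply the existing exclusion for a lifetime AN or BN diagnosis to linked NPR and Riksät/Stepwise diagnoses dated up to enrolment, as well as to the control question.
2. Report a sensitivity run of the Aim 3 analyses without ARIES cases who have elevated PEDE-Q weight- or shape-concern scores (assuming the instrument yields them separately). The sponsor should set the cut-off before the data are analysed. Describe any change in the ARFID–AN estimate; do not make the conclusion depend on both runs agreeing. With one sixth of cases affected, the estimate may move little either way.

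Removing cases who receive an AN diagnosis after enrolment should be exploratory at most. It conditions on a future outcome and may remove true ARFID cases who carry liability shared with AN, which would lower the estimate.

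The cost is a slightly smaller case group and one extra run. No new recruitment, questionnaire or sampling is needed.

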#### Hypotheses

Sensory-based food avoidance will be genetically related to autism, low appetite to depression and metabolic factors, and fear-based avoidance to anxiety and OCD. We also expect the genetic associations of ARFID with neurodevelopmental conditions and anxiety to be stronger than the genetic associations of ARFID with other EDs.

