##### Phenotypic analyses

We will describe the ARFID sample to present demographics; ARFID symptoms, onset and course; other ED pathology; food intake; co-occurring psychiatric, neurodevelopmental and somatic conditions and traits; treatment utilisation; environmental exposures; impairment and quality of life; and parental stress and ED pathology. Depending on the distribution, we will compute mean/SD or median/IQR for continuous variables, and *N*/percent for categorical variables. To compare ARFID cases with controls on all outcomes, we will conduct generalised linear modelling.

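### Controls, but not cases, are screened for psychiatric diagnoses and for eating disorders in first-degree relatives, so case-control tests on those diagnoses are fixed by selection and tests on correlated outcomes are biased

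*Protocol article*

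**What the plan says.** **Controls.** The Case definition text says controls must "have no lifetime diagnosis of any ED or other psychiatric condition, and who have no first-degree relatives with an ED". Table 1 in the same section lists "No first degree relative with a lifetime diagnosis of any ED", but words the psychiatric criterion as "No current diagnosis of a psychiatric disorder". Text and table therefore differ on lifetime against current.

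**Cases.** Apart from the PEDE-Q limits (EDE-Q in Table 1), cases need only "have no lifetime diagnosis of AN or BN". No other psychiatric diagnosis and no family history of ED excludes a case.

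**Hypothesis.** Under Aim 1, "we expect participants with ARFID to report more co-occurring psychiatric, neurodevelopmental and somatic conditions than participants without ARFID".

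**Analysis.** The Phenotypic analyses section lists co-occurring conditions and parental ED pathology among the measures, then states: "To compare ARFID cases with controls on all outcomes, we will conduct generalised linear modelling". The Aim 1 paragraph is slightly narrower and promises comparison for most variables. The Data analysis section adjusts for age and sex/gender and corrects for multiple testing.

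**The concern.** A variable that was used to select one group is then tested as an outcome between the groups. A control with a screened diagnosis cannot exist, whereas a case with one stays in. The groups would differ even if ARFID had no relation to psychiatric illness. The same holds for diagnosed ED in a parent.

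Adjusting for age and sex does not undo selection on the outcome. A multiplicity correction raises the bar for significance but leaves the bias in place. The article exempts no screened variable from the comparison, and its strengths and limitations do not mention the asymmetry.

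At stake is the psychiatric part of a stated Aim 1 hypothesis. It could be reported as confirmed when the result comes from the eligibility rule.

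**Working it through.** **Inputs from the article:** 1500 cases and 500 controls (Participants); the selection rules (Case definition, Table 1); standardised effect 0.2, 80% power and 394 per group (Statistical power). **Assumptions:** all prevalences, shares of diagnoses that are current, and correlations below. Significance is two-sided at 0.05 unless stated. Rejection rates in steps 3 to 5 count only significance in the expected direction, so an unbiased test would show 2.5%.

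**1. The plan's own figure.** n per group = 2(1.96 + 0.8416)²/0.2² = 392.4, so 393; the t-based solution is 393.4, so 394. This matches at alpha 0.05. The printed alpha of 0.5 would give 2(0.6745 + 0.8416)²/0.04 = 114.9, so 115. That discrepancy is separate and does not bear on this point; 0.2 serves below only as a yardstick.

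**2. Screened psychiatric diagnoses.** Controls are fixed at 0/500. Fisher's exact test gives p = 0.076 for 11/1500 cases and p = 0.045 for 12/1500 (0.8%). The false-rejection rate with no true association is P(X ≥ 12), X ~ Binomial(1500, prevalence). With a Bonferroni correction for an assumed 20 tests (0.0025), the threshold rises to 22 cases.

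| Assumed prevalence | Rejection at 0.05 | Rejection at 0.0025 |
|---|---|---|
| 0.5% | 8% | about 0% |
| 1% | 82% | 5% |
| 2% | over 99.9% | 95% |
| 3% | over 99.9% | over 99.9% |

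**3. Lifetime diagnoses if only current ones are screened (Table 1).** Let p be the lifetime prevalence and s the share that is current. The rate in screened controls is p0 = p(1 − s)/(1 − ps), and the spurious odds ratio is 1/(1 − s): 1.33, 2.0 and 4.0 for s = 25%, 50% and 75%. At p = 10%, p0 is 7.7%, 5.3% and 2.7%, and the null is rejected 32%, 93% and about 100% of the time.

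**4. Conditions not screened but associated with psychiatric diagnosis** (somatic; neurodevelopmental if not counted as psychiatric). Let p be the condition's prevalence, ps the prevalence of psychiatric diagnosis, and OR their association. The joint probability a solves a(1 − p − ps + a) = OR(p − a)(ps − a), and the control rate is (p − a)/(1 − ps).
- OR 1: no bias.
- p = 10%, ps = 20%, OR 5: control rate 6.25%, spurious odds ratio 1.67, rejection 74%.
- Across OR 2 to 10, p 5–10% and ps 10–20%: spurious odds ratio about 1.1 to 2.6, rejection 5% to 99%.

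**5. Scales, such as parental ED symptoms.** If the top fraction q of a normal liability is removed from controls and the scale correlates r with it, the shift in SD units is r·φ(z)/(1 − q), where z is the upper-q normal quantile and φ the normal density. The standard error is √(1/500 + 1/1500) = 0.0516.
- q = 2%, r = 0.3: 0.3 × 0.0484/0.98 = 0.015; rejection 5%.
- q = 10%, r = 0.5: 0.5 × 0.1755/0.90 = 0.097; rejection 47%.
- q = 10%, r = 1: 0.195; rejection 97%. This is close to the 0.2 the study is sized for, but it requires diagnosis to track the scale perfectly.

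**The case against.** The strongest reply is that this reaches less far than it first appears. Much of the reply stands.

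- **The whole comorbidity hypothesis cannot fail.** A reader might infer this. The documents do not support it. Somatic conditions are not screened in main-study controls. Neurodevelopmental conditions are listed apart from psychiatric ones throughout, and the article does not say that the exclusion covers them. Hypotheses on onset, course and ARFID presentation can be tested within cases and are unaffected.
- **The parental comparison is settled in advance.** The listed measure is parental ED pathology, not diagnosed ED. Excluding diagnosed relatives biases a symptom score but does not determine it (step 5). Only a comparison of diagnosed parental ED is fixed.
- **Child ED pathology is equally affected.** Table 1 applies the same global-score, vomiting and laxative limits to both groups. Only the binge limit and ED diagnoses other than AN and BN differ.
- **The genetic comparisons are tilted too.** Aim 4 expects the "genetic associations of ARFID with neurodevelopmental conditions and anxiety to be stronger than the genetic associations of ARFID with other EDs", and it is tempting to say that the screening favours that ranking. This is not shown. ARIES supplies 500 of the roughly 62,000 meta-analysis controls (about 0.8%), and the Discussion bases the cross-disorder work on the combined data.
- **Only most variables are compared, and fuller analysis plans exist.** True, but the Aim 1 wording does not say that the screened variables are the ones left out, and the Phenotypic analyses section says all. The article itself fixes the selection rule, the hypothesis and the contrast, and these three conflict.
- **Multiplicity correction protects.** It does for rare diagnoses: 5% rejection at 1% prevalence with 20 tests. At 2% the rate is still 95%.

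**Conclusion.** The point holds in a bounded form. The contrasts on the screened psychiatric diagnoses and on any diagnosed ED in a parent are fixed by selection: controls are 0/500, 12 of 1500 cases reach p<0.05, and with no true association the false-rejection rate is about 82% at 1% prevalence and over 99.9% at 2% or more. It is only 8% at 0.5%. The prevalences are assumptions; the zero in controls follows from the eligibility rule.

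If Table 1's current-diagnosis rule governs, lifetime contrasts are strongly biased rather than fixed (odds ratio 2.0 if half of lifetime diagnoses are current). Psychiatric traits, correlated somatic conditions and parental ED symptoms are biased away from the null, from negligibly to severely depending on their correlation with the screened diagnoses. Neurodevelopmental contrasts belong in this group unless the exclusion counts them as psychiatric, in which case they are fixed as well.

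**What to change.** 1. Remove the screened variables (psychiatric diagnoses; diagnosed ED in parents or other first-degree relatives) from the hypothesis tests of cases against ARIES controls, and describe them in cases. Test the Aim 1 psychiatric comorbidity hypothesis only against a reference not screened on psychiatric status, if one is available. The linkage described in the article covers the study's own data, so population rates would have to be obtained separately.
2. For symptom scales, correlated conditions and parental ED symptoms, keep the full contrast. Add a sensitivity contrast that applies the control exclusions to cases, and state in the limitations that the full contrast is biased away from the null. The restricted contrast should stay secondary: it has fewer and less typical cases, and the Recruitment section aims for a group that represents ARFID in the population.
3. Reconcile lifetime in the text with current in Table 1, and state whether neurodevelopmental diagnoses count as psychiatric for the control exclusion.

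The cost is wording and a few extra models. No new participants are needed and control eligibility need not change; changing it during recruitment would mix two control definitions.
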